### Outcome measurements

#### Definition of primary and secondary outcomes

The primary outcome is number of days spent at home (or in the same care home) in the 90 days following randomisation [10]. This is calculated as 90 days minus days spent dead, in hospital, intermediate care, or a new care home.

It is assumed that discharge home and successfully maintaining it is the goal of health care in this context, taking account of mortality, and readmission, and is a suitable high level summary of the success or failure of hospital acute care.

Secondary outcomes are:

• Mortality

• Quality of life, measured using the dementia-specific Demqol patient and proxy scales [23]; Euroqol EQ5D [16]; and short London Handicap Scale [24]

• Behavioural and psychological symptoms (Neuropsychiatric Inventory [18])

• Carer satisfaction with hospital care (from [2])

• Physical disability (Barthel index [17])

• Cognitive impairment (Mini-Mental State Examination [14])

• Readmission, and total hospital length of stay

• Place of residence

• New care home placement

• Carer strain index [20]

• Carer psychological distress (GHQ-12 [21])

• Health and social care resource use, using the Client Service Receipt Inventory [25] and from routine health and social care records.

#### Ascertainment of outcomes

Outcomes are measured using:

• a brief telephone call to carer one to three weeks after patient discharge to complete questions on satisfaction with care

• interview of the patient and carer participants at home 90 days (± 7 days) after randomisation

• telephone call to GP or community nurses at 90 days (± 7 days) for community service use

• scrutiny of the hospital computer records for mortality, and readmission

• interrogation of computerised routine health and social care records held by: general and mental health hospitals, general practice, adult social care departments, intermediate and other community based health care, and the ambulance service.

Outcome assessments are done by research staff who were not involved in recruitment or baseline data collection, and who are not deliberately aware of group allocation. They are therefore 'blind' to allocation.

### Withdrawal

Patients and carers are free to withdraw from the follow up study without detriment to their care on the MMHU, standard wards, or during follow up. A request to be transferred off the MMHU would be negotiated case by case. Patients allocated standard care have no access to the MMHU.

### Data analysis

#### Power and sample size

We used data from the prior cohort study to estimate sample size and statistical power. The Days at Home variable has a negatively skewed distribution (median 62 days at home, inter-quartile range 1 to 82 days), with 24% of participants having zero days at home. We assumed that the Mann-Whitney U test would be used to test for differences between groups. We used a bootstrapping simulation method to investigate the power of the study to detect possible effects of the MMHU, on both the probability of zero days at home and numbers of days spent there, under a range of plausible assumptions. A study with 300 participants in each group has 80% power to detect a 5 day difference in days at home, if the proportion of patients with zero days at home is reduced to 20% (a 15% reduction). This represents a reasonable minimum clinically important difference.

#### Data handling and analysis

Data are double entered into a secure Access database (Microsoft, Redmond, WA).

#### Descriptive statistics, univariate and multivariate analyses

Baseline and outcome data for each treatment group will be presented as follows: continuous data that are approximately normally distributed will be summarised in terms of the number of observations, mean, standard deviation, minimum and maximum. Skewed data will be transformed to normality, if possible, or otherwise presented in terms of the number of observations, median, lower and upper quartiles, minimum, and maximum. Categorical data will be summarised as frequency counts and percentages.

We will compare baseline differences between groups descriptively to explore whether there are differences in the characteristics of those recruited in the MMHU and standard care groups. The design of this study, with recruitment following randomisation, means that baseline differences may occur that have not arisen by chance, and we will therefore also carry out statistical significance testing of differences at baseline, using parametric or non-parametric tests, as appropriate to the distribution of measured variables.

Analyses of primary and secondary outcomes will be by intention to treat including all those recruited, and will compare differences between MMHU and standard care:

• Mean/median days at home, and total length of hospital stay (and 95% confidence intervals for the differences)

• Proportions dead, at home, in new care homes and readmitted (and 95% confidence intervals for the differences)

• Mean/median scaled outcomes for patients and carers (and 95% confidence intervals for the differences).

• Quantitative and qualitative analysis of the non-participant observer study.

• Proportions of participants receiving various assessment and interventions recorded in the case notes (and difference in proportions with 95% confidence intervals).

Multiple linear, logistic, Poisson and Cox regression will be used, as appropriate to the error distribution of each outcome variable, to model the difference between treatments, adjusting as appropriate for apparent baseline differences, and for other prognostically important variables to improve the precision of effect estimates. We will explore the fit of alternative statistical models for days at home, which will take account of the non-standard distribution of this variable constrained to take values between zero and 90 days, and with an excess of zero values. Non-parametric continuous data will be transformed to normality where possible or otherwise analysed using Mann Whitney U-test. The intervention effect parameter will be presented as an estimate with 95% confidence intervals.

We will use imputation methods for dealing with missing values from those who withdraw, die, or otherwise do not provide follow-up data. We will conduct sensitivity analyses to explore the robustness of the results to alternative assumptions about the randomness of missing data.

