**Figure 1 F1:**
[figure not shown]
**Randomisation and bed management algorithm**. Patients with codes <4000 are randomised with stratification according to care home residence or not, and are approached for trial inclusion. Patients with codes >4000 are not randomly allocated, and are not eligible for trial inclusion.

Research staff monitor the list of randomly allocated patients, and, as soon as they can be contacted, invite them, and a carer, to take part in the trial. If they agree, baseline data are collected. Satisfaction with care is recorded by the carer one to three weeks after discharge; other outcomes are ascertained by interview 90 days after randomisation. Quality of care and patient experience are assessed by observation. Resource use is collected by questionnaire, and from electronic service records.

The trial flow diagram is given in Figure 2.

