## Discussion

### Justification for design

The study design had to accommodate the constraints of an acute medical service very pressed for bed availability, and under rigorous performance management of patient flows, in particular, the government-prescribed maximum four hour Emergency Department wait target. This stipulates that all patients must be assessed, treated, and discharged or transferred from Emergency Departments (ED) within four hours of arrival. This, in turn, puts pressure on Acute Medical Admissions Units, who must have empty beds to accept transfers from ED, and on wards to have capacity to accept patients from Admission Units.

It was, therefore, unacceptable to the clinical service for potential trial participants to remain on the Acute Medical Admissions Unit whilst awaiting research assessment or recruitment procedures, or for there to be more than three empty beds on the MMHU. It had to be possible to admit to the MMHU 24 hours a day and seven days a week, regardless of researcher availability, and to keep the ward full with appropriate patients. Proper time for consultation, consent or consultee agreement for research participation to be given, is necessary for legal and ethical reasons. The consultation and consent process takes longer than the clinical processes for swift bed management. So it was impossible to run a conventional randomised controlled trial with recruitment prior to allocation: clinically patients had to be allocated before they could be recruited.

Previous work demonstrated that 30% of acute medical patients over 65 had cognitive impairment, far more than could be accommodated on a single ward. Some allocation mechanism was therefore required by the clinical service. In usual clinical practice, ward allocation is largely driven by bed availability, but in this case the service agreed to allocate suitable patients at random, either to the MMHU, or standard care on another general or geriatric medical ward.

The allocation algorithm ensures that the MMHU remains acceptably full, without compromising recruitment to the trial. Only patients who have been randomly allocated, and their carers, are invited to participate in the trial.

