### Implications of design

Strictly, the design violates best practice for a randomised controlled trial, since only randomised patients who consent, or have consultee agreement, can be followed up. For this reason, we have chosen to describe it as a 'controlled clinical trial'. However, it approximates to a pragmatic, parallel group, randomised controlled trial.

The main scientific concern about the design is failure to recruit a patient after randomisation. This introduces the potential for bias (for example, if it proves easier to recruit from one setting than the other). Baseline data cannot legally or ethically be collected for research purposes from randomised patients who do not consent (or have consultee agreement) to take part.

Despite the risk of differential recruitment bias, an important consideration is that this design enables us to undertake a trial at all. A conventional randomised controlled design would either have failed because of conflict with the demands of the clinical service, or would have recruited an unrepresentative population. If we attempted to recruit with inadequate consent or consultation, the trial would be illegal, and would be open to bias through high withdrawal rates.

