### Additional measures to avoid bias

Studying people in urgent care settings unavoidably carries risk of bias. We introduced explicit steps to try to minimise that risk.

Researchers are aware of potential problems with bias, and are trained to adopt a rigorous approach to recruitment, whilst respecting an individual's right not to be involved in research if they so choose, or if circumstances (such as end of life care) make it inappropriate.

Research staff operate shifts to be available when family carers are visiting, to maximise recruitment. A contact log is maintained. The proportion of randomised patients recruited in each setting is monitored closely.

Extensive data is collected at baseline from recruited participants that will enable comparison of groups, and statistical adjustment for baseline imbalances if found.

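### The set called intention to treat contains only patients recruited after allocation, and the analyses stated for it cannot show how far unequal recruitment could move days at home

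*Protocol article*

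**What the plan says.** All references are to the protocol article.

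- **Analysis set.** Under Descriptive statistics, univariate and multivariate analyses: "Analyses of primary and secondary outcomes will be by intention to treat including all those recruited".
- **Order of events.** Under Justification for design: "clinically patients had to be allocated before they could be recruited". Under Overview of study design, below Figure 1: "Research staff monitor the list of randomly allocated patients, and, as soon as they can be contacted, invite them, and a carer, to take part".
- **Who is followed up.** Under Implications of design, "only randomised patients who consent, or have consultee agreement, can be followed up". The same section adds: "Baseline data cannot legally or ethically be collected for research purposes from randomised patients who do not consent".
- **The authors' own view.** The same section states: "The main scientific concern about the design is failure to recruit a patient after randomisation". For this reason they do not call the study a randomised controlled trial.
- **Operational response.** Additional measures to avoid bias lists researcher training, shifts timed to carers' visits and a contact log. It also states: "The proportion of randomised patients recruited in each setting is monitored closely".
- **Analytic response.** Because recruitment follows randomisation, "we will therefore also carry out statistical significance testing of differences at baseline". Regression then adjusts for imbalances that are found. Imputation and sensitivity analyses deal with missing values from patients who withdraw, die or give no follow-up data.

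**The concern.** Intention to treat protects a comparison because every randomised patient is counted in the allocated arm. Here a patient is counted only if recruited, and the treatment setting could influence recruitment. The article gives several reasons to take this seriously:

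- The Medical and Mental Health Unit (MMHU) is one ward, while standard care is spread over four geriatric and six general medical wards.
- Most candidates lack capacity, so a relative or carer usually has to act as consultee. Closer work with families is itself part of the MMHU intervention.
- The 90-day count starts at randomisation. The prior cohort's upper quartile is 82 days at home, so about a quarter spent at most 90 − 82 = 8 days away from home. The time in which to reach such patients in hospital can be short.
- End of life care is accepted as a reason not to approach a patient.

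Patients who die early score zero or close to it, and those discharged early score close to 90. Unequal loss of either kind acts directly on the primary outcome. Tests, adjustment and imputation within the recruited set cannot measure what was lost outside it.

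**Working it through.** **1. The label against the sequence.** Allocation comes first, consent or consultee agreement second, and follow-up only for those with agreement. The analysed set is therefore conditioned on a post-randomisation event. Analysing patients as allocated is kept; counting everyone randomised is not.

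**2. The plan's own benchmark.** Under Power and sample size, 300 per group gives 80% power for a 5-day difference, with zero-day patients falling from 24% to 20%. I rebuilt the distribution from the stated figures (24% zeros, quartiles 1, 62 and 82) with an assumed maximum of 88, and simulated the Mann-Whitney test at an assumed two-sided 5% level:

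- 20% zeros plus a 3-day shift in the rest (mean difference 4.8 to 5.0 days): 72% power.
- 20% zeros plus a 4-day shift (mean difference about 5.6 days): 85 to 86% power.

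The stated 80% lies between these. It is plausible and is not in dispute. The 5-day target is used below only as a yardstick.

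**3. Rebuilt mean.** With straight lines between the stated quantiles:

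0.24×0 + 0.01×1 + 0.25×(1+62)/2 + 0.25×(62+82)/2 + 0.25×(82+88)/2 = 0 + 0.01 + 7.875 + 18 + 21.25 = 47.14 days.

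A second interpolation shape gives about 48.3.

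**4. Shift in one arm's mean from excess loss in that arm.** Let p be the excess share of randomised patients lost and y their days at home. The recruited mean becomes (47.14 − p·y)/(1 − p). If p is lost at 0 days and another p at 85 days, it becomes (47.14 − 85p)/(1 − 2p). The 85 is the midpoint of 82 and 88.

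| Lost in one arm only | p = 5 points | p = 10 points |
|---|---|---|
| Zero-day patients | 47.14/0.95 = 49.62, **+2.5** | 47.14/0.90 = 52.38, **+5.2** |
| 85-day patients | 42.89/0.95 = 45.15, **−2.0** | 38.64/0.90 = 42.93, **−4.2** |
| Both, p of each | 42.89/0.90 = 47.66, **+0.5** | 38.64/0.80 = 48.30, **+1.2** |

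The 10-point zero-day case means missing 10/24 = 42% of all such patients in one arm beyond the other, which is a lot.

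**5. Effect on the test when there is no true effect** (2,000 simulated trials per scenario, 300 recruited per arm):

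- MMHU alone loses 5 points of zero-day patients (5/24 = 20.8% of them). Its zero-day share falls to (0.24 − 0.05)/0.95 = 20%, the very shift the design assumes. The false gain is about 2.5 days, with 13 to 15% rejection at a nominal 5%.
- Standard care alone loses 20% of its patients with 82 days or more: about 2.0 days, 13 to 14% rejection.
- Both arms lose 20% of each type: about 5% rejection, so equal loss does no harm.

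The cancellation in the last row of the table was worked out for the mean. It was not simulated for the rank test.

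**The case against.** The strongest reply is that nothing is hidden. The disputed sentence itself says who is analysed, and the article concedes that the design departs from best practice and avoids the usual trial label. A reader might infer that the authors overlooked or concealed the problem; the text does not support that. The operational measures also act on differential recruitment at source.

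Second, the article is condensed. An analysis plan that is not shown could hold a bounding analysis, and the trial flow diagram, also not visible, may provide for counts by arm. This stands. The lack of a tipping-point analysis is not a fault in itself. What can be said is that the responses stated here do not reach the problem named here.

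Third, the one-sided shifts are worst cases. If one arm is simply harder to reach, it would tend to lose early deaths and early discharges together, and the table shows these largely offset. Those who refuse may have any outcome. The planned subgroup with an index stay of 5 days or less implies that short-stay patients are recruited. This also stands.

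Fourth, baseline comparison is not useless. Loss of the sickest patients from one arm could show in illness severity, disability or delirium scores. It would be too strong to call the bias undetectable; baseline data may reveal part of it but cannot measure the missed outcomes.

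The label is not rescued by any of this, because disclosure elsewhere does not give a recruited-only set the property that the term claims.

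**Conclusion.** The point holds in limited form. The label is wrong for the set it describes, and this rests on the article's text alone. The stated analyses stay within the recruited set, so they cannot show how far differential non-recruitment could move the primary result.

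The size is unknown. The scenarios run from about +0.5 day (both types lost equally in one arm, 5 points each) to about +2.5 or −2.0 days (one type only, 5 points), against a 5-day target. They rest on a rebuilt distribution, an assumed maximum of 88 days and assumed loss rates. Early death and early discharge before recruitment are inferred mechanisms: the article names easier recruitment in one setting, and end of life care.

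A reader might infer that selection could account for the whole 5-day target. That needs a one-sided excess of about 10 points, or opposite kinds of loss in the two arms, and the document gives no evidence of either.

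**What to change.** 1. **Rename the set** as recruited patients, analysed as allocated, and drop the intention-to-treat label.
2. **Report numbers randomised and recruited** by arm and care-home stratum. Give reasons for non-recruitment (died, discharged, declined, consultee declined, not reached) as aggregate counts, where the screening and contact logs record them.
3. **Pre-specify a tipping-point analysis of days at home.** For each arm, the mean over all randomised patients is r·ȳ + (1 − r)·m, where r is the recruited fraction, ȳ the recruited mean and m the assumed mean of those not recruited. Vary m by arm and state the between-arm difference in m that would overturn the conclusion. Set deaths before recruitment to 0 days only where aggregate counts are lawfully available.

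This can support the result as well as weaken it. With equal r in both arms, an observed difference D is brought to zero only if m differs between arms by D·r/(1 − r) in the opposite direction. For an illustrative D of 5 days, that is 5×0.95/0.05 = 95 days at 5% non-recruitment, which is impossible on a 90-day scale. At 10% it is 5×0.90/0.10 = 45 days, and at 20% it is 5×0.80/0.20 = 20 days.

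The cost is a little more analysis work. No contact with non-consenting patients and no individual data on them are needed, but what the logs hold and what may be released from them must be confirmed. The conclusion may have to be worded more cautiously.

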### Secondary hypotheses

Compared with standard care, management on the MMHU will be associated with:

1. lower mortality

2. better quality of life, less behavioural disturbance, and less disability after 90 days

3. fewer readmissions, reduced total hospital stay over 90 days, and fewer new care home placements

4. greater satisfaction with hospital care amongst family carers

5. less carer strain and psychological dysfunction.

Management on the MMHU is cost-effective compared with standard care.

Management on the MMHU is associated with better quality of care and patient experience in a concurrent observational study.

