#### Economic analyses

Costs will be constructed from the perspective of the NHS and personal social services. Ninety days of resource data will be collected for each patient participant. Costs for each participant will be calculated as resource use multiplied by the unit cost of the specific resource, valued using published unit cost data.

A cost-effectiveness analysis comparing the MMHU to standard care will be carried out using standard methods. Incremental cost-effectiveness analysis will be undertaken in the absence of convincing dominance by any treatment alternative. Benefits to the patient participant will be measured with Quality-Adjusted Life Years (QALYs), which will be generated using EQ5D data, assuming homogeneity across treatment groups in any insensitivity of the EQ5D to our patient participants. These will be combined with cost data to generate Incremental Cost-Effectiveness Ratios and Incremental Net Benefit statistics. No discounting will be necessary given the short follow-up time.

Sensitivity analyses and cost-effectiveness acceptability curves will be used to assess uncertainty in the estimated incremental net benefit statistics.

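### Death is put under the same imputation rule as withdrawal, so day-90 patient scale scores would be imputed for patients who have died

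*Protocol article*

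**What the plan says.** All references are to the protocol article.

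- **Missing data** (Descriptive statistics, univariate and multivariate analyses): "We will use imputation methods for dealing with missing values from those who withdraw, die, or otherwise do not provide follow-up data". No outcome is exempted and no method is named. The next sentence adds: "We will conduct sensitivity analyses to explore the robustness of the results to alternative assumptions about the randomness of missing data".
- **Analysis set** (same section): primary and secondary outcomes are analysed by intention to treat in all recruited participants. Patient and carer scales are compared as means or medians.
- **Timing** (Ascertainment of outcomes): patients and carers are interviewed at home 90 days after randomisation, within 7 days either way. Mortality comes from hospital computer records.
- **Hypotheses** (Secondary hypotheses): the first is "lower mortality" and the second is "better quality of life, less behavioural disturbance, and less disability after 90 days". Cost-effectiveness is also hypothesised.
- **Primary outcome** (Definition of primary and secondary outcomes), on days at home: "This is calculated as 90 days minus days spent dead, in hospital, intermediate care, or a new care home".
- **Mortality analysis** (Descriptive statistics section): "Proportions dead, at home, in new care homes and readmitted (and 95% confidence intervals for the differences").
- **Economics** (Economic analyses): "Benefits to the patient participant will be measured with Quality-Adjusted Life Years (QALYs), which will be generated using EQ5D data". No rule for death is given.

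**The concern.** A patient who withdraws still has a quality of life and a level of function at day 90; they are simply not observed. A patient who has died has neither. Imputation is a sensible answer to the first situation. In the second it supplies values for a quantity that is not defined.

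This matters because the trial hypothesises both a survival benefit and better day-90 quality of life and disability. If the unit keeps more patients alive and the dead in both arms receive scores like those of survivors, the scale comparison contains no trace of that benefit. If survival is equal, the scale means still describe a group that partly does not exist. QALYs would be distorted in the same way if EQ5D values imputed under this rule were used to build them.

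**Working it through.** The plan gives no figure on this point that could be reproduced: there is no mortality rate, no EQ5D level and no count of expected missing values. The check therefore first sets the sections side by side and then gives an illustration on assumed inputs.

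**1. Which outcomes the rule reaches**

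- Demqol, EQ5D, the London Handicap Scale, the Neuropsychiatric Inventory, Barthel and MMSE are day-90 interview outcomes. None exists for a patient who died earlier, and an informant cannot report a current state either.
- Because all recruited patients are analysed and death is named in the imputation sentence, the rule covers these scales.
- The sensitivity analyses vary assumptions about how random the missingness is. That presupposes an unobserved true value, so they do not address death.
- The primary outcome treats death as observed, by subtracting days dead. The plan therefore handles death in two incompatible ways.
- The pre-planned subgroups include died v survived. If that interaction were tested on a day-90 patient scale (the article does not say for which outcomes), the whole died subgroup would consist of imputed values.

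**2. Day-90 utility**

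From the article: 300 per group. Assumed: 90-day mortality of 25% (standard care) v 20% (MMHU), the same mean utility *u* in survivors of both arms, *u* = 0.3 to 0.5, and dead patients imputed at *u*.

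- Deaths: 300 × 0.25 = 75 and 300 × 0.20 = 60, so 135 of 600 values would be imputed for dead patients.
- Death scored 0: the arm means are 0.75*u* and 0.80*u*, a difference of 0.05*u*. This is 0.05 × 0.3 = 0.015 to 0.05 × 0.5 = 0.025.
- Death imputed at *u*: both arm means equal *u*, a difference of 0.
- Overstatement of the mean: 0.25*u* = 0.075 to 0.125 in standard care, and 0.20*u* = 0.06 to 0.10 on the MMHU.

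The erased difference depends on the mortality gap and *u*, not on the mortality level. With a 5-point gap at 20% v 15% or 30% v 25% it is again 0.05*u*. With *u* = 0.4 to 0.6 it is 0.020 to 0.030.

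**3. QALYs, only if the rule is carried over**

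Assumed: baseline utility *b* = 0.3 or 0.4, day-90 survivor utility 0.5, linear change between the two, death on average at day 45 with a linear fall to 0, and a 5-point mortality gap.

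| | *b* = 0.4 | *b* = 0.3 |
|---|---|---|
| Survivor, or dead patient imputed as survivor: (*b* + 0.5)/2 × 90/365.25 | 0.1109 | 0.0986 |
| Dead patient, utility 0 from death: *b*/2 × 45/365.25 | 0.0246 | 0.0185 |
| Excess credited per dead patient | 0.0862 | 0.0801 |
| Between-arm gain removed: 0.05 × excess | 0.0043 | 0.0040 |

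The loss is about 0.004 QALY per patient over 90 days.

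**The case against.** The strongest reply has four parts.

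- **Survival is analysed elsewhere.** Mortality is a separate hypothesis and outcome, ascertained from records and compared with confidence intervals, and days dead count against the primary outcome. This stands. A reader might infer that the plan hides any survival effect; it does not. Dilution is confined to the imputed scales and possibly QALYs.
- **No imputation method is named.** A fixed or worst value for death would also be imputation, and an analysis plan not shown may settle the method. This stands as a limit on the size of the harm: survivor-like imputation is one possible method, not a stated one. It does not remove the point, because the article states a rule that groups death with withdrawal and offers no death-specific value.
- **The economic section has no imputation rule.** Its reference to standard methods may already mean utility 0 from death. This stands, so a reader cannot conclude that the plan creates QALYs for dead patients. It only leaves that possible.
- **Some missing values from patients who die are legitimate targets.** Carer strain, GHQ-12, carer satisfaction, baseline items and service use before death did or could exist. This stands, so simply deleting death from the sentence would go too far.

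Two further readings should be resisted. The 24% of the pilot cohort with zero days at home is not a mortality rate, since continuous hospital stay, intermediate care or a new care home also give zero. And the possibility that an early death shortens total hospital stay involves no imputation and is a separate matter.

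**Conclusion.** The point holds for the day-90 patient scales. The stated rule would impute scores that cannot exist for patients who have died, and the planned sensitivity analyses do not repair this. The effect on the treatment comparison depends on the method chosen. With survivor-like imputation and equal utility among survivors, a day-90 utility difference of 0.015 to 0.025 is reduced to 0, under assumed mortality of 25% v 20% and *u* of 0.3 to 0.5. If the rule also entered the QALY calculation, about 0.004 QALY per patient would be lost under the assumptions shown. None of these mortality or utility inputs comes from the article.

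The mortality comparison and the primary outcome as defined are unaffected. This is therefore a defect in the analysis of secondary patient outcomes, with a possible extension to the economic analysis, and it should be settled before the data are analysed.

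**What to change.** Replace the single imputation sentence with a rule that separates death from non-response:

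1. Impute day-90 patient scales only for patients alive at day 90.
2. In the QALY calculation, set EQ5D utility to 0 from the date of death.
3. Report the other patient scales in survivors, next to the mortality result, and add a rank-based sensitivity analysis with death as the worst outcome. The survivor comparison alone would not show a survival benefit either, so the mortality result and the ranked analysis are both needed.
4. Keep imputation for values that did or could exist in patients who died: carer outcomes, baseline items and resource use before death.

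The cost is a change of wording and one extra analysis. The downside is that survivor comparisons use fewer patients and are conditional on survival, so they lose the protection of randomisation if mortality differs between arms; the report should say so.
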